## Abstract

**Background:**

Preliminary clinical studies on the single-implant mandibular overdenture (SIMO) have reported favorable results as an alternative to the conventional complete dentures for rehabilitation of the edentulous mandible. Clinical and patient-reported outcomes were assessed but no evidence is available with respect to the cost-effectiveness of this treatment, which is particularly important to test whether the incremental cost associated with the implant treatment is justified facing the benefits from the intervention. Thus, the aim of this study is to assess the cost-effectiveness of single-implant mandibular overdentures.

**Methods/design:**

This randomized clinical trial will include edentulous individuals who meet eligibility criteria. Participants will be randomized into one of the treatment groups: a conventional complete denture group or a single-implant mandibular overdenture group. Direct costs related to therapies in both groups will be identified, measured and valuated for 1 year after treatment. Oral health-related quality of life and satisfaction with the dentures will be the primary outcome variables. Incremental cost-effectiveness ratios will be estimated and graphically presented on cost-effectiveness planes. A Markov decision tree will be constructed to set out the consequences of the competing alternatives. Sensitivity analysis on the most important assumptions will be performed in order to assess the robustness of the model.

**Discussion:**

This is the first trial-based cost-effectiveness study on single-implant mandibular overdentures. Specific challenges in designing the protocol are considered. The expected results are of high clinical relevance and may contribute to the decision-making process when choosing between different alternatives for the rehabilitation of the edentulous mandible.

**Trial registration:**

ClinicalTrials.gov Identifier: NCT02710357, registered on 11 March 2016.

**Electronic supplementary material:**

The online version of this article (doi:10.1186/s13063-016-1646-0) contains supplementary material, which is available to authorized users.

## Background

Tooth loss is an important public health problem that affects different population groups, having a greater incidence in older people within disadvantaged communities [1, 2]. In Brazil, 53.7 % of the 65–74 year-old group do not have any teeth according to a national survey held in 2010 [3] and the conventional tissue-supported complete denture is still the most common clinical treatment. Although most edentulous patients appear to benefit from complete dentures and report satisfactory oral comfort and masticatory function, it is fairly frequent to find patients who are poorly adapted to their dentures, even with dentures that are perceived to be prosthodontically acceptable [4]. Individuals who experience difficulties with their dentures usually complain of pain, discomfort, poor oral coordination and limited functioning, mainly caused by low retention and stability and an unfavorable condition of the supporting tissues associated with the mandibular denture.

Proper management of unstable and uncomfortable dentures is very challenging, even for experienced prosthodontists. In most cases, the use of dental implants to retain a mandibular denture is recommended to assure a more favorable prognosis for those difficult-to-treat edentulous patients. The mandibular overdenture, retained by two implants in the interforaminal region, has been the standard of care for the edentulous mandible [5, 6]. Available evidence shows that it leads to better outcomes compared to the conventional denture, such as increased patient satisfaction and oral health-related quality of life (OHRQoL) [7]. However, there is no reliable evidence on the ideal number of implants needed to retain a mandibular overdenture [8], and the reduction of the number of implants to a single implant for denture retention has been proposed as a less invasive and less costly alternative compared to other overdenture designs [9].

The single-implant mandibular overdenture (SIMO) was originally recommended for older edentulous patients experiencing discomfort and functional difficulties with conventional mandibular dentures [10]. The implant is placed in the symphyseal region where favorable bone quality and quantity is usually found. This ensures satisfactory primary stability and high implant success rates, even for immediately loaded implants [11]. In addition, this less invasive and less costly implant intervention might allow more people to benefit from this treatment, even with general health concerns.

Previous clinical studies have shown that SIMO significantly improves patient satisfaction and improves OHRQoL impacts when compared to a conventional mandibular denture [12, 13]. Favorable results regarding several other relevant outcomes, such as higher implant survival rates, minimal marginal bone loss and acceptable incidence of adjustments and repairs, were also reported [9–18].

From an economic perspective, the available evidence strongly supports the view that mandibular overdentures retained by two or four implants are cost-effective when financers are willing to pay in excess of the calculated cost-effectiveness acceptance thresholds, considering that willingness to pay may vary considerably between financers pay within and between health care systems and outcome measures [19, 20]. The availability of simpler interventions, like SIMO, could increase the demand for implant overdentures by reducing the potential risks of surgical interventions and the incremental costs associated with the treatment in comparison to overdenture designs with greater number of implants.

The aim of this study is to assess the cost-effectiveness of the SIMO. The study hypothesis is that SIMO is more effective but more costly than the conventional denture, though this incremental cost is relatively low for the offered effectiveness in terms of clinical and patient-reported outcomes.

## Methods/design

This study is a randomized clinical trial. Study groups will include patients who are receiving a complete maxillary denture as opposed to either a conventional mandibular denture (CD – control group) or a SIMO (SIMO – experimental group). Although the two-implant mandibular overdenture is established as the standard of care for the edentulous mandible [5, 6], in most parts of the world the CD is still considered the most common treatment for edentulous patients. Therefore, we chose the CD as the reference strategy to SIMO to test the incremental effect of placing a single implant in the symphyseal region for denture retention.

A flowchart of the study is detailed in Fig. 1. The final study protocol was approved by the Research Ethics Committee of the Federal University of Goiás in September 2014 (protocol number: 020/2012). Two documents related to the reporting of clinical trials and health economic evaluations were used to guide the structure of this protocol: the Consolidated Standards of Reporting Trials (CONSORT Statement) [21] and the Consolidated Health Economic Evaluation Reporting Standards (CHEERS) [22] (see Additional file 1). All clinical procedures will be performed at the School of Dentistry of the Federal University of Goiás, Goiânia, Goiás, Brazil. Participants will not be charged for any treatment costs.

**Fig. 1 Fig1:**
[figure not shown]
Flowchart of the study

### Participants

#### Target population and sample

The target population will comprise fully edentulous subjects. The eligible participants will receive maxillary and mandibular conventional complete dentures. The primary list of participants will be retrieved from the database of registered patients in the local public health system. For the initial screening, no restrictions regarding gender and age will be considered. Treatment needs will be based on normative criteria and/or on subject’s expressed need for replacement of old dentures.

#### Inclusion and exclusion criteria

Referred subjects will be evaluated by means of a thorough clinical assessment and a panoramic radiograph. For inclusion in the study, the screened potential participants must have no contraindications for implant surgery (mainly related to uncontrolled systemic diseases) and present enough bone volume in the mandibular midline area for an implant length of at least 8 mm without the need for bone augmentation procedures. They should be able to understand and answer the questionnaires used in the study and agree to participate by providing a written informed consent.

Noncompliant participants will be excluded from the study. Moreover, individuals who do not agree to be randomly allocated to the treatment study group (CD or SIMO) will be excluded. Subjects who present signs of untreated temporomandibular disorders or uncontrolled systemic or oral conditions that require additional treatments will be referred for proper treatment and be excluded from the study.

#### Stopping criteria

A participant will be removed from the trial in case of withdrawal of the consent or discontinuation of the prescribed treatment program (deviate from protocol); for example, if the participant decides to have other implant treatment modalities during the follow-up period (such as overdentures with different number of implants and/or fixed implant dentures). Any condition preventing the attendance to follow-up visits will be considered as a participant dropout, such as incapacity due to advanced physical debilitation or moving to another city. Interrupted follow-up due to withdraw and/or dropout will be documented and consent will be sought from participants to retain data collected up to the point of withdrawal/dropout.

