### Randomization

A computer-based random number generator will be used to assign participants into the treatment groups [24]. In order to prevent imbalance between groups, participants will be stratified according to gender [25]. Block randomization will be used to randomly assign participants to sets of different sizes, using unsorted numbers with a range from 1 to 2 (representing the two treatments) and an allocation ratio of 1:1 for the control and experimental groups. The sequence will be concealed in opaque, consecutively numbered envelopes for each block. After each enrollment, the next randomization envelope will be opened, according to the previously established sequence. An independent collaborator will manage the allocation and inform participants about their assigned groups.

If a participant allocated to the SIMO group refuses to receive the implant treatment (noncompliance), follow-up will occur the same way as in the control group. Moreover, intention-to-treat analysis will be performed, which means that during statistical analysis noncompliant participants will be kept in their original group, even if they did not receive the allocated treatment. This may provide a more conservative estimation of treatment effect, minimizing the probability of type I error occurrence [26].

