### Data analysis

#### Descriptive and inferential statistics

Data will be checked and cleaned blind to the treatment group allocation and analysis will be carried out according to the intention-to-treat principle. Statistical analysis will comprise between-group comparisons of the effectiveness outcomes (OHIP and patient satisfaction) and will be performed using independent *t* tests or nonparametric tests in case of asymmetric distribution of data (IBM-SPSS 23.0 software; IBM Corp, 2015). An alpha level of 0.05 will be set for significance.

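### The stopping rule removes participants who leave their assigned treatment, so the promised intention-to-treat analysis cannot be carried out for them

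*Protocol article*

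**What the plan says.** Four places in the protocol article bear on what happens to a participant who leaves the assigned treatment.

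- **Stopping criteria:** "A participant will be removed from the trial in case of withdrawal of the consent or discontinuation of the prescribed treatment program". The rule is glossed with the words "deviate from protocol); for example, if the participant decides to have other implant treatment modalities during the follow-up period". On data already gathered, the section says that "consent will be sought from participants to retain data collected up to the point of withdrawal/dropout".
- **Inclusion and exclusion criteria:** "Noncompliant participants will be excluded from the study", with no time point.
- **Randomization:** a participant allocated to SIMO who refuses the implant is to be followed as the control group is, and "during statistical analysis noncompliant participants will be kept in their original group, even if they did not receive the allocated treatment".
- **Descriptive and inferential statistics:** "analysis will be carried out according to the intention-to-treat principle".

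Table 1 schedules both primary outcomes (OHIP-EDENT and satisfaction) at baseline, t6 and t12. Estimation of costs covers the 1-year follow-up.

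**The concern.** Intention-to-treat needs two things: participants stay in the group to which they were randomized, and their outcomes continue to be collected after they depart from treatment. The Randomization and Data analysis sections promise the first. The Stopping criteria take away the second for anyone who deviates. Data that were never collected cannot be restored at analysis, so the label would not describe what was done.

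Departure from treatment happens after randomization, and participants know their allocation. It may therefore be related to how well they are doing and may differ between arms. The two primary comparisons and the ICER would then rest on a selected subset.

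**Working it through.** **1. The rules side by side.**

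| Participant after randomization | Stopping criteria | Randomization and Data analysis |
|---|---|---|
| Obtains other implant treatment during follow-up | Removed from the trial | Kept in original group, intention-to-treat |
| Allocated to SIMO, refuses the implant | Arguably removed, as discontinuing the prescribed program | Followed as a control, kept in the SIMO group |
| Withdraws consent | Removed | No conflict |

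The first row is a direct conflict. The second is one if refusal counts as discontinuation. No sentence in the article says which rule prevails.

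**2. What is lost.** According to the Masking section, the baseline is measured before allocation is revealed. A participant removed before t6 therefore has no post-allocation primary outcome. One removed between t6 and t12 can keep t6 but has no t12. Costs stop at removal in both cases.

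**3. How much room there is.** The plan's own figure reproduces: 24 in total is 12 per arm; 12/0.9 = 13.3, rounded up to 14 per arm, or 28. Each removal is 1/14 = 7% of an arm. The 10% allowance is 0.10 × 14 = 1.4 participants per arm.

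**4. Can the bias be sized?** This illustration for OHIP-EDENT (higher is worse) rests on assumptions.

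- SD: none is stated. At 12 per arm, 80% power and two-sided 0.05, the noncentral t gives a detectable standardized difference of 1.197, so SD = 7.4/1.197 = 6.18. This assumes equal variances and that OHIP-EDENT set the sample size.
- Removing the k worst of 14 normally distributed controls improves the control mean by 0.131, 0.243 or 0.347 SD for k = 1, 2, 3. Multiplied by 6.18, that is 0.81, 1.50 or 2.14 points.
- The right comparator is full follow-up, under which those controls are scored after their outside implants. If each gains the protocol's own 7.4 units, the control mean improves by 7.4k/14 = 0.53, 1.06 or 1.59 points.
- If removal correlates only 0.5 with the score, the removal shift halves to 0.41, 0.75 or 1.07.

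| k | Removal minus full follow-up, worst scorers removed | Removal minus full follow-up, correlation 0.5 |
|---|---|---|
| 1 | 0.81 − 0.53 = +0.28 | 0.41 − 0.53 = −0.12 |
| 2 | 1.50 − 1.06 = +0.44 | 0.75 − 1.06 = −0.31 |
| 3 | 2.14 − 1.59 = +0.55 | 1.07 − 1.59 = −0.52 |

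A positive value means that removal flatters the control arm (against SIMO); a negative value means that it favours SIMO. The sign changes with an assumption that the document does not settle.

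**The case against.** The strongest defence is that the article handles the case it foresees, the SIMO refuser, correctly; that consented data are retained; and that missing-data methods may sit in an analysis plan not shown. This limits the loss but does not remove the conflict. The refuser is one kind of deviator, retained data end at departure, and an analysis plan cannot supply outcomes that the protocol told staff to stop collecting.

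Several stronger readings are tempting, and the defence is right about them:

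- **That the rule selectively drops dissatisfied controls.** It is neutral between arms, and its example also fits a SIMO participant who changes implant design. Participants come from a public-system list, and implants are not publicly covered, so outside implants within a year may be few. No rate is given.
- **That bias against SIMO reaches 11% to 29% of the 7.4-point difference** (0.81/7.4 to 2.14/7.4). This compares removal with keeping controls at their poor scores, not with following them after outside implants.
- **That removal makes the control arm look cheaper.** The main perspective is the provider's, and Table 2 lists implant, surgery and component costs as not applicable to the control arm. Implants bought elsewhere are outside that cost set even with full follow-up.
- **That the eligibility section excludes noncompliers after randomization.** The sentence stands among screening criteria, and the time between delivery of the new dentures and disclosure of allocation is one in which compliance could be judged. Against this, the Randomization section uses noncompliance for a post-allocation event. The sentence is ambiguous, not clearly wrong.
- **That treating non-attenders as dropouts is an error.** The rule "Any condition preventing the attendance to follow-up visits will be considered as a participant dropout" contradicts nothing else in the article.

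**Conclusion.** The conflict between the Stopping criteria and the intention-to-treat statements is real and rests on the text alone. Followed as written, the stopping rule prevents the stated analysis for every participant removed after randomization for deviating, through loss of later t6/t12 OHIP-EDENT, satisfaction and cost data. Each such participant is 7% of an arm of 14.

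A reader might infer a known bias against SIMO, or a known distortion of the ICER. The document supports neither. In the illustration the error relative to full follow-up runs from about 0.5 points in favour of SIMO to about 0.6 points against it for one to three removals, on an assumed SD, assumed numbers removed and an assumed 7.4-unit gain per crossover. Size and direction remain undetermined. The point is worth settling because uncollected outcomes cannot be recovered, not because a particular bias has been shown.

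**What to change.** Reconcile the Inclusion and exclusion criteria, Stopping criteria, Randomization and Data analysis sections by separating two events: departure from the assigned treatment and the end of data collection.

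- In the Stopping criteria, state that, unless consent is withdrawn, the planned t6 and t12 questionnaires and cost collection continue for every randomized participant, whatever treatment was received.
- In the Data analysis section, state that these participants are analysed in the group to which they were randomized.
- In the Inclusion and exclusion criteria, state that the noncompliance sentence applies only before randomization.

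This concerns follow-up and analysis only and takes no position on clinical care. Recruitment began in March 2016, so the change should reach sites before further t6 and t12 data are lost. The cost is a change of wording, slightly more follow-up work, and a treatment contrast diluted by any crossover. Dilution of that kind is part of what an intention-to-treat comparison estimates.

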### Sample size estimation

In this study, sample size was estimated for each of the two treatment groups considering a minimum power of 0.80 (type II error rate) at a two-sided 0.05 significance level (type I error rate). A previous single-group clinical trial that assessed the incremental effect of the SIMO treatment compared to the CD, and considered the outcome satisfaction with the dentures and OHRQoL, served as the data source for this sample size estimation [23]. A minimum of 24 patients will enter this two-treatment parallel-design study, considering that the true difference between treatments is 7.4 units for OHIP-EDENT and 2.6 units for satisfaction scores, assuming unequal variances for both groups. An increase of 10 % to reduce the impact of loss to follow-up on study power resulted in a minimum final sample of 28 participants, 14 in each treatment group.

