### Outcomes

The effectiveness of both treatments will be measured by means of two primary patient-centered outcomes: oral health-related quality of life (OHRQoL) impacts and satisfaction with the dentures:OHRQoL impacts: the cross-culturally adapted Brazilian version of the Oral Health Impact Profile for edentulous subjects (OHIP-EDENT) will be used [31, 32]. It contains 19 items divided into four different subscale domains: (I) masticatory discomfort and disability (four items), (II) psychological discomfort and disability (five items), (III) social disability (five items) and (IV) oral pain and discomfort (five items). The items are answerable on a 3-point Likert scale and responses will be summed to obtain an overall OHIP-EDENT score and for each of the four domains. Higher scores represent worse OHRQoLSatisfaction with the dentures: a 10-cm uninterrupted Visual Analog Scale will be used in order to assess the participants’ ratings of their satisfaction with the upper and lower dentures in relation to the parameters “general satisfaction,” “comfort,” “stability,” “aesthetics,” “ability to speak,” and “ability to chew.” Each participant will indicate their level of satisfaction with each parameter by marking a point along the scale, in which one end signifies “unsatisfied” and the other end signifies “satisfied,” respectively. Then, an assistant will convert each mark into a value of between 0 to 100 by placing a transparent template with numbered intervals from 0 to 100 mm.

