Dental materials	Overall consumable resources/cases	Microcosting	Mean market prices	Yes	Yes
Instruments/equipments					
Conventional denture	Estimation of lifespan for each item	Estimated annual costs	Panel of specialists	Yes	Yes
Implant/overdenture	Estimation of lifespan for each item	Estimated annual costs	Panel of specialists	No	Yes
Nondental direct costs					
Transportation fares	Number of visits per patient	Self-reported	Cost from public transportation	Yes	Yes

*CD* conventional mandibular denture, *PPE* personal protective equipment, *SIMO* single-implant mandibular overdenture

Overall costs for the two alternative treatments will include the summative value of all direct costs listed in Table 2. The currency used for cost estimations will be Brazilian reals – BRL R$. Price date will be recorded and values will be adjusted to the year of the registered costs by applying specific price indexes. If currency conversion is required for the final report, purchasing power parity (PPP) will be used to equalize the purchasing power of different currencies by eliminating the differences in price levels between countries. Alternatively, a widely used currency, such as the US dollar, will be adopted for cost estimations.

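### The dropout rule ends collection of the patient-reported primary outcomes for anyone who becomes unable to attend, although those outcomes can reasonably be obtained without attendance

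*Protocol article*

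**What the plan says.** The rule is in Stopping criteria: "Any condition preventing the attendance to follow-up visits will be considered as a participant dropout, such as incapacity due to advanced physical debilitation or moving", where the second example is relocation. The same paragraph adds that "consent will be sought from participants to retain data collected up to the point of withdrawal/dropout". It describes no later collection of any outcome.

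The Outcomes section names "two primary patient-centered outcomes: oral health-related quality of life (OHRQoL) impacts and satisfaction with the dentures". On the OHIP-EDENT it says: "The items are answerable on a 3-point Likert scale and responses will be summed to obtain an overall OHIP-EDENT score". It does not say whether the 19 items are self-completed or read out by an interviewer, or where this happens. The satisfaction VAS is marked by the participant and converted to a number afterwards by an assistant using a template. Table 1 schedules both instruments at baseline, t6 and t12.

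Sample size estimation deals with loss to follow-up through numbers only: "An increase of 10 % to reduce the impact of loss to follow-up on study power resulted in a minimum final sample of 28 participants", 14 per group. Randomization and Descriptive and inferential statistics both commit to intention-to-treat.

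**The concern.** Dropout is defined by inability to come to the clinic, and dropout ends follow-up for every outcome. Yet the measures that clearly need the chair are the chewing-gum test, implant stability, peri-implant bone level and soft-tissue examination, and none of these is primary. The needs of the secondary and implant measures therefore end collection of the two primary ones.

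Three things are at stake. A trial of 28 loses 12-month primary data that it could probably have obtained. One of the two named triggers is a health state, so the participants who remain may differ from those lost in a way related to the outcome. And an analysis that keeps everyone in the group to which they were randomised has no 12-month value for participants whose follow-up was closed under the rule.

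**Working it through.** **1. The plan's own figure.** Inputs from Sample size estimation: 24 participants (12 per arm), two-sided alpha 0.05, power 0.80, 10% allowance.

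- 12 / (1 − 0.10) = 13.3, rounded up to 14 per arm.
- 12 × 1.10 = 13.2, also rounded up to 14 per arm.

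Both routes give 28, so the stated figure reproduces. The 24 itself cannot be re-derived, because the article gives no standard deviation.

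**2. What the allowance covers.** Assumption: the true standardised effect d is the one that gives exactly 80% power with 12 v 12 in a two-sided t test. Solving gives d = 1.197, which implies an SD of 7.4 / 1.197 = 6.18 OHIP-EDENT units. Power is taken from the noncentral t distribution with n1 + n2 − 2 degrees of freedom and noncentrality d / √(1/n1 + 1/n2).

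| Lost of 28 | Share lost | Arms | Power |
|---|---|---|---|
| 0 | 0% | 14 v 14 | 86% |
| 3 | 10.7% | 13 v 12 | 82% |
| 4 | 14.3% | 12 v 12 | 80% |
| 6 | 21.4% | 11 v 11 | 76% |
| 8 | 28.6% | 10 v 10 | 72% |

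If three are lost from one arm only (14 v 11), power is 81%; with four (14 v 10) it is 79%. The allowance therefore does its job for about 3 to 4 losses. Remote collection could at most bring power back towards 86%.

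**3. What the allowance does not cover.** If a fraction f of one arm is lost, and the lost participants' mean is worse than that of those retained by g SD, the observed mean of that arm is too favourable by f × g SD. The values of f and g below are assumptions; the document gives neither.

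- Smallest case: f = 1/14, g = 0.5: 0.071 × 0.5 = 0.036 SD, or 0.036 × 6.18 = 0.22 OHIP-EDENT units.
- Largest case: f = 3/14, g = 1.0: 0.214 × 1.0 = 0.214 SD, or 0.214 × 6.18 = 1.32 units.

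Against the planned difference of 7.4 units this is 3% to 18%. It applies when loss falls in one arm only. If loss is similar in both arms, the shift largely cancels in the comparison.

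**4. Can the primary outcomes be had without attendance?** For the VAS, the text points to yes: the participant makes the mark and the template reading comes later, so a returned sheet can be scored in the same way. For the OHIP-EDENT it is an inference from its form (19 items, three response options) and from the inclusion requirement that participants can understand and answer the questionnaires.

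**The case against.** The strongest reply is that this is a design preference. There is no numerical error, the plan allowed for loss, and power stays near 80% within that allowance. Retention procedures and missing-data handling are commonly left to a full protocol or SAP. All of that is fair, and it limits the weight of the point. It does not remove it, because the article does not leave the matter open: it states a rule that closes follow-up.

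A reader might infer more than the document supports:

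- *That one missed visit makes a dropout, so that someone ill at t6 is barred from t12.* The rule speaks of a condition preventing attendance at visits, and its examples are lasting ones. Temporary incapacity is simply not addressed.
- *That the SIMO arm must lose more participants, having more appointments.* Surgery, suture removal and the 3-week loading step are treatment steps, not clearly follow-up visits. At most t1 is an additional contact in that arm. Differential loss is not shown.
- *That only frail participants are lost.* Relocation is named as well, and need not be related to health.
- *That costs could be rescued by telephone.* Table 2 values follow-up in clinician minutes, with laboratory units and consumables. The item it marks as reported by the participant is travel: "Transportation fares Number of visits per patient Self-reported". A telephone call would not restore the remaining costs, so the cost side of the ICER would stay incomplete for these participants.
- *That the rule contradicts intention-to-treat.* Randomization describes that principle as keeping noncompliers in their original group, which the dropout sentence does not deny. The tension is practical. A SIMO participant who refuses the implant is followed as in the control group, while a treated participant who moves away is not followed at all.

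Remote collection also does not abolish selection, since some frail or relocated participants will not respond.

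**Conclusion.** The point holds as an inexpensive improvement to a stated rule. Under Stopping criteria, inability to attend ends collection of both patient-reported primary outcomes, although they can reasonably be obtained without attendance. That is well supported for the VAS and is an inference for the OHIP-EDENT.

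Each loss is 1/14, or 7%, of an arm. The effect on power is small within the allowance (86% with no loss, 82% with three lost, 80% with four), under an effect size back-solved from 12 per arm. What remains uncovered is selection related to health. In the assumed one-arm example this moves an arm by about 0.2 to 1.3 OHIP-EDENT units against 7.4. Between-arm bias is a risk only if loss differs by arm; the document gives no evidence that it will.

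**What to change.** In Stopping criteria, state that a participant who cannot attend but has not withdrawn consent remains in follow-up for the primary outcomes. Specifically:

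- Obtain the OHIP-EDENT and the VAS sheet by post or similar remote return within the 6- and 12-month windows. The OHIP-EDENT may be taken by telephone if needed, with the participant's own answers and not a proxy's. The VAS needs a physical or equivalent mark, so a telephone call does not serve for it.
- Keep anyone who misses t6 due for t12.
- Ask about denture events and care received elsewhere.
- Record the mode of collection for each assessment.

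This changes data collection only. The cost is modest: mailing the questionnaires and some calls. The downside is a possible mode effect in a few participants. Masticatory performance, the implant measures and most clinic-measured follow-up costs will still be missing for them, and the analysis should say so.

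The preceding sentence in the same section, on removal for discontinuing treatment or deviating from protocol, is a separate matter outside this change. It should be reconciled with the intention-to-treat statements on its own.
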